**K. Planned use of linked data (if applicable):**

We intend to use CPRD data linked with HES in patient data to enable optimal stroke, MI, and major bleeding ascertainment, and ONS mortality data to determine deaths. When matching CPRD patients we plan to include the practice level deprivation level index as a matching variable because socioeconomic status is predicted to influence the likelihood of the primary study outcome of stroke.

[figure not shown]

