- no severe comorbid condition with life expectancy of  $\leq 1$  year,
- no active alcohol or drug abuse, or significant psychosocial difficulties (e.g., psychosis, dementia),
- no recent ischemic stroke (within 7 days),
- no severe renal insufficiency (serum creatinine > 2.5 mg/dL or a calculated creatinine clearance < 25 mL/min),
- no ALT or AST > 2X ULN or a Total Bilirubin  $\geq 1.5$ X ULN (unless an alternative causative factor such as Gilbert's syndrome is identified),
- no platelet count  $\leq 100,000/\text{mm}^3$ ,
- no haemoglobin < 9 g/dL,
- no prior exposure to apixaban,
- no women who are pregnant or breastfeeding

For the 3 criteria involving patient laboratory results (renal insufficiency, low platelet count, and low haemoglobin) a patient will be excluded if their last test result in the 90 days prior to the index date meets the exclusion criteria.

**Step 2:** Next we will determine if/when these patients received apixaban or warfarin. Individuals in EHR who have more than one warfarin eligibility period within their record will be able to contribute more than once to the pool of warfarin subjects (with the covariates and person-time contributed unique to the specific eligibility period) as long as they have no past apixaban exposure.

**Step 3:** Having obtained individual level patient data for ARISTOTLE participants from Bristol Myers-Squibb we will then match each ARISTOTLE apixaban participant 1:1 with the closest available apixaban patient record in our EHR pool. We will consider matching on a selection of the following ARISTOTLE baseline characteristics:

- age
- sex
- body mass index
- systolic blood pressure (mmHg)
- history of congestive heart failure or left ventricular systolic dysfunction

[figure not shown]

- hypertension requiring pharmacological treatment
- diabetes mellitus
- prior stroke or TIA or thromboembolism
- smoking status [current smoker, former smoker, or never smoked]
- alcohol consumption [none, low, moderate, heavy]
- renal impairment [severe, moderate, mild, normal based on the CrCL value]
- prior VKA/warfarin use
- concomitant treatment with:
  - anticoagulant/VKA use other than warfarin or apixaban
  - aspirin
  - antiplatelets
  - NSAIDs
  - lipid lowering drug therapy
  - CYP3A4 inhibitors

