We anticipate matching all or the majority of ARISTOTLE apixaban subjects with an EHR patient, giving us a pool of ARISTOTLE-analogous apixaban patients, with similar baseline characteristics as ARISTOTLE subjects at the point of randomisation (n~9,000).

The variables selected as potential matching variables are those known or suspected to influence the likelihood of the outcomes of interest. The exact selection of matching variables will depend on the quality and completeness of the data available and a balance will be struck between the matched sample size and sample balance. Variables may be grouped together to increase the sample size, for example by grouping concomitant medications that increase bleeding risk. Continuous variables may be coarsened by splitting into appropriate categories. A procedure will be employed to facilitate selection of a matched cohort, for example via coarsened exact matching for example by use of the %CEM SAS macro. Coarsened Exact Matching is a nonparametric matching method that has been found to give estimates of casual effects with lower variance and bias for a given sample size compared with other commonly used methods of matching.

Figure 1: Assembly of Matched Trial-analogous Cohort of EHR Patients

[figure not shown]

Step 4: The resulting trial matched sample of EHR apixaban exposed subjects will be matched to the warfarin ARISTOTLE-eligible EHR subjects (Figure 1) using a matching method such as propensity score matching (PSM), or CEM (with the final method selected based upon method giving the optimal sample size versus balance). Where an individual from EHR has multiple warfarin “eligibility periods” that can be matched to an apixaban trial matched subject, the EHR characteristics that will be matched on will be those from the beginning of the specific eligibility period. The covariates for consideration in the matching between EHR treatment arms or construction of a PS model will include the variables listed above used in in step 3 along with additional EHR variables such as data source (CPRD Gold or Aurum), socioeconomic status, and comorbidities. The hazard ratio for the outcomes of interest (listed in section N) will then be calculated. Each apixaban patient from the ARISTOTLE-eligible EHR

[figure not shown]

patients will be matched 1:1 with the warfarin EHR patient with the closest match giving a trial-analogous analysis cohort of ~18,000.

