#### **o Censoring**

##### Index date

The index date for the EHR cohort will be the date of the patient's first prescription of apixaban or warfarin (for objectives 1 and 2), or for objective 3 first prescription of apixaban, warfarin, rivaroxaban, or dabigatran on or after the date the patient first met the eligibility criteria for the trial in the treatment period of interest

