##### Treatment Switching and Discontinuation

[figure not shown]

As the primary analysis accounts neither for treatment switching nor for treatment discontinuation and does not capture that these may be unfavourable outcomes both the proportion of patients discontinuing treatment and time to treatment discontinuation will be tabulated by prescribed treatment.

o Regression model

Hazard ratio (apixaban/warfarin) comparing the event rate (%/yr).

Interpretation: This estimand targets the treatment-policy effect of treatment initiation of apixaban vs initiation or continuation of warfarin on the time to first stroke or systemic embolism.

All time to event endpoints will be analysed using a Cox proportional hazards model including treatment group as a covariate and prior warfarin/VKA status (experienced, naïve).

Point estimates and two-sided 95% CIs for HR will be constructed for the outcome.

o Validation of Observational Results Against Aristotle Data

In Objective 1 alone we will validate the findings from our primary analysis against ARISTOTLE by determining whether results of the EHR analysis are compatible with the ARISTOTLE trial results. The ARISTOTLE trial demonstrated superiority of apixaban over warfarin for the primary endpoint (HR 0.79, 95% CI 0.66-0.95). The treatment effect seen with the EHR data may be weaker than that seen in ARISTOTLE.

A subgroup analysis looking at the outcomes of the EU patients in ARISTOTLE showed a smaller treatment difference with the estimate for HR below 1 but upper limit of the CI crossing 1 for the primary efficacy endpoint and death: HR for stroke/SE = 0.92 (95% CI = 0.56; 1.52), HR for all cause death = 0.89 (95% CI = 0.68; 1.18). It was suggested in the European Medicines Agency (EMA) Assessment Report that the smaller treatment effect seen in the EU patients could be due to better INR control in the warfarin arm of the EU subgroup (median TTR 68.93%). This study could provide additional evidence on this point. Since all the patients in our cohort are from the UK the results can be compared with the results from the ARISTOTLE patients in the EU.

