#### **P. Plan for addressing confounding**

In the EHR cohort study period apixaban was a newly available treatment for the indication of interest leading to the possibility of channelling bias. The analysis cohort in this study is derived from observational data meaning there is likely to be confounding. To handle confounding for all objectives the treatment arms will be matched using the optimal method selected, for example by propensity score matching or coarsened exact matching. For objective 1 by applying the trial inclusion and exclusion criteria to both treatment cohorts and matching using the baseline covariates we should avoid channelling bias. It is possible that unmeasured or unknown confounding may remain and this will be explored and discussed in the analysis of the results.

[figure not shown]

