#### **T. Limitations of the study design, data sources, and analytic methods**

Some of the criteria that should be assessed for ARISTOTLE eligibility may not be well recorded in CPRD. Criteria such as “increased bleeding risk” are vague and it is not clear exactly which Read codes should be included and time scale considered. Other criteria such as alcohol and drug abuse may not be captured for all patients in CPRD. These limitations are consistent with our aim to select a population as similar as possible to the ARISTOTLE trial population with the acknowledgment that differences will remain. The most important risk factors for the primary outcome of stroke (the components of the CHA2DS2-VASc score for AF stroke risk of age, sex, history of congestive heart failure, hypertension, stroke/TIA history, vascular disease history, and diabetes) are mostly well recorded in CPRD.

There are differences in the coding systems used by the two datasets and it is possible that the completeness of coding differs between the two. The potential impact of the different coding systems and completeness of coding will be ascertained by comparisons of the rates of diagnoses, events, baseline variables (such as smoking status, alcohol use, lab values, and vital signs), and prescriptions of interest. Including the data source (Gold or Aurum) as one of the matching variables should prevent discrepancy between the two datasets from biasing the results.

The main focus of the study is the validation of our methodology through assembling a cohort of patients comparable to the patients included in ARISTOTLE and finding similar results to the trial. Criteria to determine the success of the methodology have been pre-specified in the protocol. Given the use of CPRD data to determine treatment effectiveness is not yet well established, a finding that these data are not suitable to answer questions on intended effectiveness will be a useful conclusion.

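### Mid-treatment warfarin users can be paired with later apixaban switchers on an undated prior-VKA flag, so the claim that matching should avoid channelling is not supported

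*Protocol*

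**What the plan says.** All references are to the Protocol.

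- **Contrast** (section O, Regression model): the "treatment-policy effect of treatment initiation of apixaban vs initiation or continuation of warfarin". Continuation is deliberately part of the comparator.
- **Index date** (section O): the first prescription of either drug "on or after the date the patient first met the eligibility criteria for the trial in the treatment period of interest". Section L opens the window on 1 January 2013, the month in which apixaban was authorised for this indication, and closes it provisionally on 31 January 2019.
- **Prior VKA**: a candidate matching variable given only as "prior VKA/warfarin use" (section L, Step 3), and a two-level term in the "Cox proportional hazards model including treatment group as a covariate and prior warfarin/VKA status (experienced, naïve" (section O).
- **Match between arms** (section L, Step 4, repeated in section N): the Step 3 variables "along with additional EHR variables such as data source (CPRD Gold or Aurum), socioeconomic status, and comorbidities". Calendar time of index, time since warfarin start and INR before index are not named. INR time in therapeutic range appears only as an adherence measure and an exploratory subgroup.
- **Confounding** (section P): channelling is recognised because apixaban was new, and the protocol then states that "by applying the trial inclusion and exclusion criteria to both treatment cohorts and matching using the baseline covariates we should avoid channelling bias". The next sentence allows that unmeasured confounding may remain.

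**The concern.** Among patients on warfarin when the window opens, the index rule can place a continuing user in early 2013, part-way through treatment. A patient who moves from warfarin to apixaban is indexed at the switch, which may be years later. Both are VKA-experienced, so the flag treats them as exchangeable. They can differ in calendar period, in time already spent on warfarin and in how well INR was controlled before index, which may be why one stayed and the other left. Section O itself cites INR control as a possible reason for the smaller effect in the trial's EU patients, so the protocol regards it as relevant to this hazard ratio. Randomisation balanced such factors in ARISTOTLE; no named matching variable does so here.

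The hazard ratio must fall between 0.69 and 0.99 for the method to count as validated, and Objectives 2 and 3 then reuse that method.

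**Working it through.** The protocol gives no index-date distribution, share of experienced patients, stroke trend or event count, so there is no figure of its own to reproduce. The first check is textual; the rest are illustrations on stated assumptions.

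**1. Following the text exactly.** Take a patient continuously on warfarin since before 2013 and eligible at the start of the window. The index rule gives an index date at the first in-window prescription. Take a similar patient who switches to apixaban in 2016 (an invented year). Both carry the value experienced. No named variable separates them by date, time on warfarin or past INR, so they can be paired.

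**2. Secular trend.** Assumed: continuing users are indexed evenly over the first three months (mean 0.125 years), and apixaban starts are uniform over the window.
- Window length: 6 + 30/365.25 = 6.08 years.
- Mean gap: 6.08/2 − 0.125 = 2.92 years.
- Factor on the hazard ratio in experienced pairs = (1 − yearly fall)^2.92. At 1%, 3% and 5% this is 0.97, 0.92 and 0.86.
- With a share *s* of experienced pairs and no gap in naive pairs, the overall factor = (1 − yearly fall)^(2.92 × *s*):

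| Yearly fall | s = 0.3 | s = 0.5 | s = 0.7 |
|---|---|---|---|
| 1% | 0.991 | 0.985 | 0.980 |
| 3% | 0.974 | 0.957 | 0.940 |
| 5% | 0.956 | 0.928 | 0.901 |

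A true hazard ratio of 1 would be shifted below the 0.99 limit in every cell except the mildest.

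**3. The opposite direction.** Assumed: switchers carry a 20-30% higher hazard and half the pairs are experienced. A true 0.79 becomes 0.79 × 1.2^0.5 = 0.87 to 0.79 × 1.3^0.5 = 0.90. The two mechanisms can offset each other, so the net sign is not known.

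**4. Effect on the validation rule.** The ARISTOTLE interval 0.66-0.95 gives SE = ln(0.95/0.66)/(2 × 1.96) = 0.093, or about 4/0.0929² = 463 events. Assume the same information here and a true hazard ratio of 1. The log hazard ratio is then normal with mean ln(bias factor) and SE 2/√events. The probability of meeting both criteria (estimate in 0.69-0.99 and upper limit below 1.52) is:

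| Bias factor | 300 events | 463 events | 800 events |
|---|---|---|---|
| 1.00 | 47% | 46% | 44% |
| 0.97 | 57% | 59% | 61% |
| 0.94 | 67% | 71% | 77% |
| 0.91 | 76% | 82% | 88% |

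The first row shows that much of this chance exists without any bias, because the upper bound lies so close to 1. Only the rise down each column belongs to the present point.

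**The case against.** **The covariate list is open.** Steps 3 and 4 offer variables for consideration and give examples, and the final set may be fixed in a SAP that is not at hand. This stands: the protocol does not exclude calendar time, and the accurate statement is that it is neither named nor required. But the index rule and the two-level flag are stated in the protocol, and the pairing described above can arise even when both are followed.

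**Not every experienced patient fits the picture.** The flag has no recency condition, so some experienced apixaban patients may have stopped warfarin long before. Step 2 lets a person contribute several warfarin eligibility periods, so later index dates are possible. Both points stand. They rule out saying that every experienced pair sets a fresh switcher against a continuing user. No passage, however, gives an uninterrupted user a later index date.

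**Section P concedes residual confounding, and prior VKA is both a matching candidate and a model term.** True, so channelling is partly controlled. The concession names no method.

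A reader might infer more than the documents support:
- *That bias certainly stays in the hazard ratio, or that its size is known.* Every magnitude here is assumed.
- *That vascular disease is left out.* Section T counts it among the main stroke risk factors ("stroke/TIA history, vascular disease history, and diabetes") and the Step 3 list lacks it, but Step 4 adds comorbidities, which can cover it.
- *That deprivation is measured wrongly.* Section K says "we plan to include the practice level deprivation level index as a matching variable". Patient-level deprivation is also requested, but it covers England only, so the practice-level index is a defensible choice.
- *That unequal follow-up is itself a bias.* Under proportional hazards and independent censoring, it does not bias a Cox hazard ratio.

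**Conclusion.** The point holds in limited form. It is firm, from the text, that the comparator includes continuing users, that they can be indexed mid-treatment near January 2013, that prior VKA is an undated use/no-use variable, and that no named matching variable covers calendar time, time on warfarin or earlier INR control. Section P's expectation that channelling should be avoided does not follow from those variables.

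How much bias results is not established, nor is its direction. The overall factor of roughly 0.90-0.99 rests on an assumed 1-5% yearly fall in stroke rate, a gap of about 2.9 years, 30-70% experienced pairs and no gap in naive pairs. Biases of that size would matter because a true null needs a factor of only 0.99 to reach the edge of the acceptance window. The change should be made before the analysis.

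**What to change.** 1. **Step 4 and the index rule together.** Match on prior-VKA status and on calendar period of index (year or half-year). Within VKA-experienced pairs, also match on time since first warfarin prescription. Amend the index-date rule so that a continuing warfarin user can be indexed at a later eligible prescription, with eligibility and covariates taken at that date. Without this amendment, calendar matching would leave later switchers short of experienced comparators.
2. **INR.** Include pre-index INR control where recorded, at least as a balance check or sensitivity analysis. The protocol does not state how complete pre-index INR is, so it should not be a condition of entry to the match.
3. **Reporting.** Give the primary hazard ratio separately for VKA-naive and VKA-experienced pairs, beside the overall result.
4. **Section P.** Say that eligibility criteria and matching may reduce channelling bias, rather than that they should avoid it.

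**Cost.** Items 1 and 3 use prescription dates that the study already needs. Time since first warfarin prescription can only be counted from the first one in the record. Some apixaban patients may go unmatched, which could move the cohort away from its trial-matched target; the number lost should be reported. The trial-eligible Gold counts in section I, 45,435 warfarin against 8,407 apixaban, give 5.4 to 1 and make tighter matching plausible. They do not guarantee it, because they precede the exclusions for missing BMI or blood pressure and no warfarin count is given for Aurum.

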By assessing superiority and non-inferiority we will see whether the treatment effect observed is more similar to the study results as a whole (apixaban superior) or the EU subgroup results. Either a result of superiority or non-inferiority will be considered compatible with the ARISTOTLE trial results. We have set two criteria that must be met for us to conclude results are consistent with the result demonstrated in the trial:

1. The effect size must be clinically comparable with the ARISTOTLE findings; the hazard ratio for time to stroke/systemic embolism with the EHR must be between 0.69 and 0.99. This range is not symmetrical around the ARISTOTLE estimate of 0.79 as it is anticipated that the treatment effect in routine clinical care may be weaker than that seen in the optimised setting of a clinical trial.

2. The upper limit of the 95% confidence interval for the rate ratio must be less than 1.52 (upper limit in the EU subgroup of ARISTOTLE).

In addition, if the upper limit of the 95% CI is less than 1 then superiority of apixaban vs warfarin will be concluded. Either result (superiority or non-inferiority) will be taken as evidence that EHR data may be useful to look at NOACs

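### Whether superiority is reached is used to decide if the EHR effect resembles the whole ARISTOTLE trial or its EU subgroup, but that status depends on the number of events as well as on the effect

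*Protocol*

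**What the plan says.** All of this is in Protocol section O, mostly under Validation of Observational Results Against Aristotle Data.

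- **The benchmarks.** Whole trial: "The ARISTOTLE trial demonstrated superiority of apixaban over warfarin for the primary endpoint (HR 0.79, 95% CI 0.66-0.95". EU subgroup: "HR for stroke/SE = 0.92 (95% CI = 0.56; 1.52". The EU result is described as one that "showed a smaller treatment difference with the estimate for HR below 1 but upper limit of the CI crossing 1".
- **The INR link.** A regulatory assessment report is cited for the suggestion that better INR control in the EU warfarin arm explains the smaller effect. The protocol adds: "This study could provide additional evidence on this point".
- **The rule.** "By assessing superiority and non-inferiority we will see whether the treatment effect observed is more similar to the study results as a whole", and the sentence goes on to set the two alternatives as "apixaban superior) or the EU subgroup results".
- **The test behind it.** "if the upper limit of the 95% CI is less than 1 then superiority of apixaban vs warfarin will be concluded". The interval is the one in the regression paragraph: "Point estimates and two-sided 95% CIs for HR will be constructed for the outcome".
- **The validation criteria, which are separate.** The EHR hazard ratio must lie between 0.69 and 0.99, and the upper 95% limit must be below 1.52. Superiority and non-inferiority both count as compatible with the trial.

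This text names no direct comparison of the EHR hazard ratio with 0.79 or with 0.92. It says only that the UK results can be compared with those of the EU patients.

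**The concern.** Which of two hazard ratios an estimate resembles is a question about the distance from each, judged against the uncertainty. The protocol answers it with a test against 1. Whether an interval excludes 1 depends on the effect and on the number of events together. The same hazard ratio can thus fall on the EU side in a small cohort and on the whole-trial side in a large one.

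Two errors follow. With modest event numbers, a cohort whose true effect is 0.79 may fail to reach superiority and be described as EU-like. With more events, a cohort whose true effect is 0.92 may reach superiority and be described as whole-trial-like. A larger cohort changes which error is likelier; it does not repair the rule.

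At stake is the interpretation of Objective 1. Because the EU comparison is introduced together with the INR-control explanation, an imprecise result could be presented as support for that explanation.

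**Working it through.** **Inputs from the protocol.** HR 0.79 (0.66 to 0.95) and 0.92 (0.56 to 1.52); two-sided 95% CI; superiority if the upper limit is below 1; consistency range 0.69 to 0.99 and upper limit below 1.52 (section O). Matching is 1:1 with about 18,000 patients (section L, Objective 1, Step 4). The only sizing figures are feasibility counts, and they reproduce: 0.60 × 23,526 = 14,115.6, and 14,115 + 8,407 = 22,522 (sections I and J).

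**Assumption.** No event rate, mean follow-up or event count is given. I take 1.0 to 2.0% per year and 1.5 to 3 years of mean follow-up:

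- low: 18,000 × 0.010 × 1.5 = 270 events
- high: 18,000 × 0.020 × 3 = 1,080 events

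**Step 1: precision of the benchmarks.** SE(log HR) = ln(upper/lower)/3.92; equivalent events at 1:1 = 4/SE².

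- Whole trial: ln(0.95/0.66)/3.92 = 0.0929, about 463 events.
- EU subgroup: ln(1.52/0.56)/3.92 = 0.2547, about 62 events.

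**Step 2: how often the rule mislabels.** With D events, SE = 2/√D, and superiority needs an estimate below exp(−1.96 × SE). For true hazard ratio h, P(superior) = Φ((−1.96 × SE − ln h)/SE). At 463 events the cut-off is exp(−1.96 × 0.0929) = 0.833. The fourth column also requires the estimate to be within 0.69 to 0.99. The 1.52 limit never binds for such estimates once there are about 84 events.

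| Events | Estimate needed for superiority | True HR 0.79: not superior | True HR 0.79: not superior, both criteria met (read as EU-like) | True HR 0.92: superior (read as whole-trial-like) |
|---|---|---|---|---|
| 270 | 0.788 | 50.9% | 47.7% | 10.1% |
| 300 | 0.797 | 46.8% | 44.2% | 10.8% |
| 463 | 0.833 | 28.2% | 27.5% | 14.4% |
| 600 | 0.852 | 17.7% | 17.4% | 17.4% |
| 1,000 | 0.883 | 3.9% | 3.8% | 26.1% |
| 1,080 | 0.888 | 2.8% | 2.8% | 27.8% |

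**Step 3: the label can contradict the estimate.** An estimate of exactly 0.79 is not superior below (3.92/ln 0.79)² ≈ 277 events. The log-scale midpoint of the benchmarks is √(0.79 × 0.92) = 0.853. Below (3.92/ln 0.853)² ≈ 604 events, some estimates nearer to 0.79 than to 0.92 are not superior. Example at 463 events: HR 0.84 has CI 0.70 to 1.01 and would be called EU-like, yet ln(0.84/0.79) = 0.061 is smaller than ln(0.92/0.84) = 0.091.

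**Step 4: can the benchmarks be told apart?** The EU interval contains the whole-trial interval. The EU share of the information is 0.0929²/0.2547² = 0.133. Removing it gives an implied non-EU HR of exp[(ln 0.79 − 0.133 × ln 0.92)/0.867] = 0.772, with SE 0.0998. EU against non-EU: z = ln(0.92/0.772)/√(0.2547² + 0.0998²) = 0.64, p = 0.52.

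The gap between the benchmarks is ln(0.92/0.79) = 0.152. With an EHR cohort of unlimited size, an EHR HR of 0.92 differs from the trial's 0.79 by z = 0.152/0.0929 = 1.64. An EHR HR of 0.79 differs from the EU 0.92 by z = 0.152/0.2547 = 0.60. With 463 EHR events these fall to 1.16 and 0.56.

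**The case against.** The strongest reply is that no decision depends on this sentence. Superiority and non-inferiority both count as compatible, and moving on to Objectives 2 and 3 rests on the two numbered criteria. That stands, and it limits the point to interpretation. A reader might infer that the validation verdict itself is compromised; the protocol does not support that.

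A reader might also infer that every non-significant result is read as EU-like. It is not: a non-significant hazard ratio outside 0.69 to 0.99 fails the first criterion and is inconsistent with the trial. The fourth column of the table allows for this, and the figures change little.

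Nor is the mapping of non-superior to EU-like spelled out; only the superior side is glossed in parentheses. But the sentence offers two alternatives and one assessment to choose between them, so this is the natural reading. Hazard ratios and CIs will be reported, so readers could make their own comparison, and an SAP could add a method. Neither changes the rule that the protocol states.

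A reader might further infer that a non-superior result is to serve as the evidence on INR control. The protocol says only that the study could add evidence. Section O (Sensitivity analyses) plans a more direct examination, with time in therapeutic range by Rosendaal's method and an exploratory subgroup analysis by TTR category.

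Finally, the size depends on an unstated event count. At the top of the assumed range the first error is only about 3%, and the second stays below 30% throughout. It would be wrong to say that a true EU effect is usually mislabelled.

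**Conclusion.** The point holds for the interpretive conclusion only. Superiority status does not measure similarity to either benchmark. Assuming 270 to 1,080 events, a true HR of 0.79 misses superiority about 51% down to 3% of the time. If both consistency criteria must also be met, the range is about 48% down to 3%. A true HR of 0.92 is labelled whole-trial-like about 10% up to 28% of the time.

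These figures rest on the assumed event range, 1:1 groups and a normal approximation to the log hazard ratio. The EU against non-EU comparison uses only the published intervals and treats the subgroup as a fixed share of the trial's information. Since even an unlimited EHR cohort would not separate the benchmarks at the 5% level once their own uncertainty is counted, cannot distinguish is a likely honest answer, and the rule has no place for it. This should be corrected, but it does not block the study.

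**What to change.** In Protocol section O, Validation of Observational Results Against Aristotle Data, replace the sentence on superiority and non-inferiority with wording such as:

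> Similarity to the overall and EU results will be described by the ratio of the EHR hazard ratio to each ARISTOTLE hazard ratio (0.79 and 0.92), each with a 95% CI that includes the uncertainty of both estimates. These ratios will be reported as estimates; if both CIs include 1, the study will be reported as unable to distinguish the two. Presence or absence of superiority will not be used for this purpose.

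The variance of each log ratio is the sum of the two squared standard errors. The benchmark standard errors are 0.0929 and 0.2547. A rule that asks only whether the EHR interval excludes 0.79 or 0.92 should be avoided, because it treats those estimates as known constants and brings back a label driven by cohort size.

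In the paragraph on the EU subgroup, add only that a non-superior result will not by itself be taken as evidence for the INR-control explanation, which will be examined through the TTR analyses already planned under Sensitivity analyses.

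The two validation criteria stay as they are. The cost is a wording change and two ratios from estimates already planned or quoted, with no new data. The downside is that the study will more often report that it cannot tell the two benchmarks apart.
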